#### Plans to give access to the full protocol, participant-level data and statistical code {31c}

Public access will be granted to the full protocol, participant-level dataset and statistical code.

#### Composition of the data monitoring committee, its role and reporting structure {21a}

Given that the trial drugs are licensed products with acceptable safety profiles in more than 30 million children in Central and West Africa [31], a formal Data Monitoring Committee (DMC) will not be constituted. Nevertheless, if a suspected drug-related adverse event is reported to the study staff, the event will be investigated by a local safety monitor who will be an experienced paediatrician based in Senegal. S/he will visit the child’s home to examine the child and interview the parents/caregivers, meet with health staff and check health centre records and complete an adverse event form and report. The local safety monitor will report the findings to the sponsor of the study. If the safety monitor, investigators or sponsors have any safety concerns (e.g. death or severe generalised skin reactions), an independent panel of three malaria and NTD researchers will review severe and serious suspected adverse drug reactions and data from all inpatient records for children admitted to the hospital for at least 24 h within one month of SMC administration to evaluate severity and possible relationship with the study drugs. The description of how SAEs will be recorded is provided below.

#### Adverse event reporting and harms {22}

For the primary endpoint on safety and tolerability of the combined drugs, active surveillance will be used for the collection and collation of adverse drug reactions and adverse events such as vomiting, skin rash, body weakness, etc. Trained field workers, under the supervision of the investigators, will visit all enrolled children irrespective of the study arms, daily at home starting from the evening of days 0 till 3 days after completion of the first cycle of SMC course, to collect adverse events and adverse drug reactions using a purpose-designed electronic diary card. In the context of a pandemic, if travel or home visit is not possible, these follow-up visits may be done by video or telephone call. In the event that the field worker finds any grade 3 (severe) solicited symptoms, the participant will be brought to the nearest health centre or health post for examination by a study clinician.

During the field worker visits, the children’s parents/caregivers will be asked retrospectively if any medical event that might be a serious adverse event (SAE) occurred since the last visit and this information will be recorded in the diary card. Unreported SAEs detected in this way will be investigated and reported by the PI or delegate on the corresponding SAE reporting form. If a study participant is reported to be unwell at the time of a visit, the field worker will advise the parent/caregiver to report to Saraya health centre or the nearest health post, where a member of the study team will be notified for follow-up. In the event that a study participant is seriously ill, appropriate referral and transfer to the nearest referral hospital will be arranged for serious illness following review by telephone or clinical review in person.

A passive surveillance system will also be implemented during the subsequent SMC cycles to complement the system described above. All study participants presenting for admission through the outpatient or emergency departments of Saraya health centre and health posts in the study villages will be evaluated. During the hospitalisation, the participant’s course of illness will be monitored to capture the symptoms and signs indicative of a severe adverse event. A blood sample for the evaluation of malaria parasites will be taken for all children attending a clinic who are reported to have had a fever within 24 h of presentation or have a measured axillary temperature of ≥37.5°C. Other possible sources of fever will also be investigated. A malaria rapid diagnosis test (RDT) will be performed to guide immediate patient management.

The investigators will evaluate any safety information that is spontaneously reported by a study participant beyond the time frame specified in the protocol. The investigators will monitor and analyse the study data including all adverse events and clinical laboratory data as they become available and will make determinations regarding the severity of the adverse events and their relation to a study drug. The investigator or clinical designee will review both adverse drug reactions and other adverse events to ensure prompt and complete identification of all events that require expedited reporting as serious adverse events.

#### Setting up of surveillance teams

A surveillance system will be established with the health centres and health posts in the study areas, before the start of the malaria transmission period, to detect and record adverse reactions and adverse events that may be related to SMC and anthelminthic drugs as implemented successfully in previous SMC campaigns in several districts in Senegal [18].

Training workshops will be conducted for staff at the health facilities on how to recognise and manage adverse drug reactions and how to document and report any adverse events suspected to be drug related. Severe skin reactions and signs of liver disease, and severe vomiting, will be highlighted as adverse events of special interest.

A purpose-designed leaflet with pictorial illustrations of the most common features of adverse drug reactions to SP, AQ, ALB and PZQ will be prepared and used for the training sessions. Copies will be distributed to all health centres and health posts in the study areas and all staff will be encouraged to use the leaflets. A reminder system will be implemented using short text messages (SMS) delivered via mobile telephones to all health centre staff reminding them to regularly look out for adverse events and to report by SMS any serious events. A phone credit will be provided to the staff as an incentive, and they will be contacted after each SMC round to confirm whether they have observed any adverse events. The health post staff will be linked to a member of the study team who will contact them by phone or in person throughout the study to maintain contact, ask about any problems, give support and advice and remind them about study procedures using a standardised list of reminders. During the period of delivery of SMC and anthelminthic drugs, unannounced supervisory visits will be made to each health centre by either the PI or a designated person to monitor compliance with adverse event reporting. A digital camera will be provided to document the occurrence of any skin rash.

During household visits to deliver the first monthly round of SMC and anthelminthic drugs, trained research assistants will explain to the parent/caregiver the purpose of the combined treatments again in simple language stating that all drugs can cause side effects in some children; that AQ may cause vomiting, and SP may sometimes cause skin reactions; ALB may sometimes cause fever and rarely sore throat; and PZQ may cause dizziness and headache but that severe problems are rare with these drugs. The parents/carers will be informed that if side effects of SMC and helminth treatments are suspected, the child should be taken to the nearest health centre or health post without delay. Trained research assistants will visit each child 1 month after each round of SMC cycle to check that there are no severe reactions to the previous treatment and to give the next round of treatment.

After each transmission period, all inpatient records from the health centres and posts will be collated for retrospective analysis for any adverse events that may be drug-related but not reported. Deaths will be investigated by verbal autopsy and reviewed for possible association with SMC and anthelminthic drugs. Serious adverse events will be reported to the national regulatory authority in Senegal within 24 h of becoming aware of it.

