## Methods: participants, interventions and outcomes

### Study setting {9}

The study will take place in villages in Saraya district, Senegal. Saraya district borders Mali to the east and Guinea to the south and is composed of the rural communities of Sabadola, Khossanto, Bembou, Missirah Dantilla, Missirah Sirimana and Medina Baffe and includes 102 villages occupying a land area of 7803 km^2^, with an estimated total population of 61,756 people, including 10, 566 under-five children and 5,770 children aged between 5 and 10 years. The Saraya department has one health centre, 10 health posts, two health huts and 39 home care providers (2019 population census estimate) (Fig. 1). Over 70% of the population live more than 15 km from a health facility. The main ethnic groups are Malinke and Diakhanke. The climate is Sudano-Sahelian with two seasons, a dry season from November to May and a rainy season from May to November. The average rainfall ranges from 16 to 4mm during these months, with an average rainfall of 213 mm during the peak period in August. Mean daily temperatures range from 14 to 36°C from July to February and 21–40°C from March to June [17]. Saraya district is one of the zones in Senegal most affected by both malaria [18] and helminths [19].

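### The referral hospital that receives seriously ill children is not among the facilities covered by passive surveillance or by the end-of-season search for unreported events

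*Protocol article*

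**What the plan says.** The statements sit in four sections of the protocol article.

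- **Adverse event reporting and harms {22}**, on a seriously ill child: "appropriate referral and transfer to the nearest referral hospital will be arranged for serious illness following review by telephone or clinical review in person".
- **Study setting {9}**, on local facilities: "one health centre, 10 health posts, two health huts and 39 home care providers". No hospital is listed.
- **Adverse event reporting and harms {22}**, on passive surveillance during the later cycles, which covers participants "presenting for admission through the outpatient or emergency departments of Saraya health centre and health posts in the study villages will be evaluated". **Setting up of surveillance teams** places the system, the staff training and the text-message reporting at the same tier of facility.
- **Setting up of surveillance teams**, on the search after the transmission period for drug-related events that nobody reported: "all inpatient records from the health centres and posts will be collated for retrospective analysis".
- **Composition of the data monitoring committee {21a}**, on the independent panel's reading of inpatient records for children "admitted to the hospital for at least 24 h within one month of SMC administration". This takes place if the safety monitor, the investigators or the sponsor have a safety concern.

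**The concern.** The end-of-season collation is the one routine step designed to find events that no one recognised or reported at the time. As written, it searches the health centres and posts and leaves out the facility to which the plan itself sends its most seriously ill children. The panel's remit does extend to hospital records, but only after a concern exists, and no routine step is described that would gather those records. The three sections therefore work with three different record scopes.

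Safety is the primary objective. There is no formal data monitoring committee and no interim analysis. Serious events are likely to be few, so completeness matters: with 200 children per arm, one event is 1/200 = 0.5 percentage points of an arm's rate.

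**Working it through.** The plan states no figure on this point. The check is a comparison of which route reaches a child treated in a referral hospital.

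| Route | Section | Period | Reaches a child treated in a referral hospital? |
|---|---|---|---|
| Daily home visits, with caregivers asked about possible serious events | Adverse event reporting {22}; Table 2 | Day 0 to day 6, first cycle | Yes, wherever the child was treated |
| Passive surveillance | Adverse event reporting {22}; Setting up of surveillance teams | Later cycles | Only if the child first presents at the health centre or a post |
| Visit to each child one month after each round | Setting up of surveillance teams | After each cycle | Yes, for severe reactions disclosed at the visit |
| Verbal autopsy of deaths | Setting up of surveillance teams | Not limited in time | Yes, with no condition on facility or length of stay |
| Panel review of suspected severe or serious reactions | Data monitoring committee {21a} | Once a concern is raised | Yes |
| Panel review of inpatient records, stays of at least 24 h | Data monitoring committee {21a} | Once a concern is raised | Yes, but not as a routine search |
| End-of-season collation of inpatient records | Setting up of surveillance teams | After the season | No: health centres and posts only |

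**Step 1: primary outcome.** The window is six days after the anthelminthic drugs (Outcomes {12}). Those drugs are given on day 0. Daily visits run until three days after the three-day SMC course, so 3 + 3 = day 6. The window lies inside the active surveillance.

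**Step 2: time outside active surveillance.** Trial status gives 17 June as the scheduled start of the first SMC cycle and 30 November as the end of follow-up. That is 13 + 31 + 31 + 30 + 31 + 30 = 166 days, of which about 160 follow the daily visits. This is the period in which the gap could arise. It does not measure the gap, because the monthly visits fall within it.

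**Step 3: who is left.** Remove, in turn, deaths (verbal autopsy), children transferred through the described referral (already known to the team through the telephone or in-person review), episodes disclosed at a monthly visit, and episodes that raised a concern (panel). What remains is a survivor whose hospital episode came after day 6, was not disclosed at a monthly visit, and prompted no concern. The likeliest case is a child taken directly to hospital.

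**Step 4: limits of the monthly visit.** It is described as a check for severe reactions to the preceding treatment, combined with giving the next round. That is narrower than the first-cycle question about any possible serious event. No further round follows the fourth cycle, and Table 2 marks no safety assessment at the end-of-season survey. The visit narrows the gap but does not close it.

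**The case against.** A reader might infer that the gravest events fall outside the safety net altogether, or that after day 6 a hospital admission enters the data only if the caregiver volunteers it. The documents do not support either reading. Every child is visited one month after each round, deaths are reviewed wherever they occur, and a child transferred by the described route has already been identified.

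A reader might also infer that the 24 h minimum stay keeps short admissions from the panel. It applies only to the inpatient-record review. Suspected severe and serious reactions go to the panel whatever the length of stay, so removing the minimum would be a preference and is not proposed here.

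Nor is it shown that serious-event counts are necessarily understated. The documents give no rate of direct hospital attendance and no reason for the gap to differ between arms, since the same facilities serve all three.

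The best remaining defence is that this is a condensed article, and that the full protocol may name the hospital and say how its records are retrieved. That lowers the weight of the point without removing it. The article does more than leave the detail open: it fixes the scope of both the surveillance and the record search at health centres and posts, and it states a different scope for the panel.

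**Conclusion.** The point holds in a narrow form. The routine search for unreported events omits the facility to which seriously ill children are referred, and the plan's three descriptions of record scope do not agree. The gap concerns non-fatal referral-hospital episodes after the first-cycle active surveillance that were not disclosed at a monthly visit and raised no concern. Ascertainment of serious events may be incomplete there. Its size cannot be derived from the documents; the only scale available is that each such event would be 0.5 percentage points of a 200-child arm. The six-day primary outcome is unaffected.

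This rests on two assumptions: that the referral hospital is a separate facility from Saraya health centre, as the facility list suggests, and that the full protocol does not already widen the collation. It is a cheap improvement, not a flaw that threatens the trial's main conclusion.

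**What to change.** In Setting up of surveillance teams, extend the end-of-season collation of inpatient records to the referral hospital or hospitals used for transfers, matched to the list of 600 participants. In Adverse event reporting and harms {22}, add the same hospital or hospitals to the passive surveillance. Then reconcile the record scope of those two sections with that of the data monitoring committee section, and say which facility is meant there by the hospital.

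The cost is one or two more record sources searched once for the season, together with the protocol wording. The downside is that hospital access permission is needed and a few more records must be read. No treatment, visit or analysis changes.

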#### Frequency and plans for auditing trial conduct {23}

The Trial Steering Group and Ethics Committee will meet to review conduct throughout the trial period.

#### Plans for communicating important protocol amendments to relevant parties (e.g. trial participants, ethical committees) {25}

Amendments of the protocol during the course of the trial will be submitted to the Research Ethics Committees of the London School of Hygiene & Tropical Medicine and the Comité National d’Ethique pour la Recherche en Santé (CNERS) in Senegal, for review and approval. The study participants and their parents/caregivers will also be informed about the changes in the study.

*Dissemination plans {31a}*

Findings of this study will be disseminated through meetings with community and religious leaders in the study site, managers at the national control programmes for malaria and neglected tropical diseases in Senegal and other stakeholders. The findings will also be presented at scientific meetings and published in a peer-reviewed journal.

## Discussion

Malaria and helminths are two parasitic diseases commonly co-existing among pre-school and school-age children in SSA [1, 3]. Following the London Declaration on NTDs in 2012, anthelminthic drugs were donated generously by pharmaceutical companies to meet the WHO target of 75% treatment coverage in pre-school and school-age children in all affected countries by 2020. Recent reports have shown that very few countries have met this target [32], and many have not demonstrated the expected impact on the prevalence of parasite infections. This shortfall is due to a combination of poor programmatic coverage, sub-optimal adherence and the exposure of parasites to sub-therapeutic drug concentrations [33].

On the other hand, seasonal malaria chemoprevention (SMC), which was recommended in the same year as the London declaration on NTDs (2012) by the WHO, has achieved more than 75% treatment coverage and prevented 75–85% cases of uncomplicated and severe malaria in children aged below 5 years in some situations [34]. The extension of SMC to children aged 5–10 years has been implemented successfully in Senegal [35] and is being considered in other West African countries. This encouraging development supports the need to explore new strategies involving integration of NTD control efforts with other successful platforms such as SMC. This integrated approach has the potential to align NTD and malaria control and elimination efforts with the SDG of ending the diseases of poverty and promote health and well-being of those at risk.

The global trend towards integrated, non-disease-specific approaches to controlling co-endemic diseases such as malaria and helminths has become an increasingly recognised strategy, but limited information exists on the safety, feasibility and effectiveness of combining SMC with helminth control at the community level [36, 37]. SMC involves administration of full treatment courses of antimalarial medications at monthly intervals during the malaria transmission to prevent malaria illness, with the objective of maintaining the therapeutic anti-malaria drug concentrations in the blood throughout the period of greatest malaria risk [31]. The approved preventive chemotherapy for mass drug administration (MDA) for STH and schistosomes (albendazole [ALB] and praziquantel [PZQ]) respectively, and the SMC drugs (AQ plus SP) work well with minimal side effects when used separately [35, 38]. Given that 4-aminoquinoline drugs are reported to have antagonistic pharmacokinetic interactions with praziquantel [39], the SMC partner drugs, AQ (a 4-aminoquinoline derivative) and SP will not be administered at the same time with anthelminthic drugs (albendazole and praziquantel) in this study. Because albendazole and praziquantel have a short half-life of 8.5 h and <2h respectively [22], anthelminthic drugs (praziquantel and albendazole) will be administered a day before the SMC drugs (AQ and SP) providing ample opportunity to objectively assess the tolerability of the different drug regimen.

The limitations of this study include the inability to mask the study drugs from parents and their children. Nevertheless, the use of control medications will ensure all study children receive equal number of medications and this could minimise bias due to unmasking. Also, the prevalence of malaria and STH is low in the study area and this may make it challenging to determine the effectiveness of the combined administration of SMC and anthelminthic drugs among the study participants but the study will provide important information on the safety and tolerability of administering SMC and antihelminthincs through a common delivery system. Measurement of efficacy is likely to require a larger study.

Overall, this study may provide evidence to boost the public health recommendations for combined malaria and helminth control. If successful, this project will reinforce the empirical evidence that the future direction of health care systems in developing countries should be comprehensive health management rather than vertical management of a single disease.

### Trial status

This paper is based on protocol version 2.0, dated 8 April 2022. Recruitment of the study participants will coincide with the commencement of the first cycle of SMC scheduled by the Senegal Ministry of Health for 17 June 2022. The recruitment was completed on 21 June 2022, and the follow-up of the enrolled participants will continue until 30 November 2022.

## Data Availability

The principal investigator and designated study personnel will have access to the final trial dataset. We disclose no contractual agreements that limit such access for the investigators.

## Abbreviations

AE: Adverse events
ALB: Albendazole
AQ: Amodiaquine
Hb: Haemoglobin
PCR: Polymerase chain reaction
PI: Principal investigator
PZQ: Praziquantel
SAE: Serious adverse event
SD: Standard deviation
SMC: Seasonal malaria chemoprevention
SP: Sulphadoxine-pyrimethamine
STH: Soil-transmitted helminths
